### Statistical analysis

With a non-inferiority trial, an intent-to-treat analysis is not necessarily conservative. For the primary outcome, we will need to provide several intent-to-treat analyses under different assumptions about patients who do not complete the trial, and a per-protocol analysis. Per-protocol analyses are planned for all secondary outcomes [44].

All outcomes will be analysed by a generalised linear model, assuming an appropriate distribution for each outcome and using the same set of covariates. These covariates will be: age, sex, education and a baseline score of the degree of restricted activity reported by the patient. 95% confidence intervals will be reported for the difference between treatment groups.

For the primary outcome, the assumed distribution will be normal; that is, analysis will be by multivariate linear regression. As a sensitivity analysis, the GP will be added to the model as a random effect and the model re-fit to the data from all GPs with only one GP per practice and with at least 10 patients per GP. Our experience from a previous trial (ISRCTN57824788) is that the difference between GPs has little influence on patient reported outcomes.

For secondary outcomes, assumed distributions will be binomial (i.e. for prescription of antibiotics) or normal (i.e. duration of antibiotic treatment). Duration of antibiotic treatment will be analysed only for those patients who receive antibiotics. We will also report a confidence interval for the difference in the antibiotic prescription rate between treatment groups. As a sensitivity analysis, we will repeat this calculation using a method appropriate for a cluster sample, where each GP forms a cluster and using only data from GPs with one GP per practice and with at least 10 patients per GP.

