**Specialisation**		
General medicine – n (%)	25 (47)	188 (54)
Internal medicine – n (%)	26 (49)	148 (43)
Other – n (%)	2 (3.8)	9 (2.6)
**Years in private practice **– median [IQR]	15 [6.2 – 20]	16 [9.0 – 23]
**Years of postgraduate training **– median [IQR]	8.8 [7.7 – 9.7]	8.9 [7.6 – 11]
**Years since diploma **– median [IQR]	25 [15 – 29]	26 [14 – 31]

When a participating GP intends to give antibiotic treatment to an eligible patient based on clinical criteria and the patient gives written informed consent, the GP calls the study centre and the patient is randomly allocated to one treatment group or the other. The GP then takes a blood sample from the patient and sends it by courier service to the laboratory of clinical chemistry at the University Hospital Basel. This laboratory measures ProCT in all patients. Additionally, the GP documents patient baseline data on signs and symptoms, diagnostic procedures, diagnosis, co-morbidity and prescribed medication.

Where patients are randomised to the ProCT-arm, GPs will be informed about ProCT results and given recommendations about appropriate antibiotic therapy within 2–4 h after the blood is taken depending on the location of the practice. A cut-off ProCT level of 0.1 μg/l is used to rule out a bacterial respiratory tract infection. This value is identical to the cut-off used for the evaluation of patients in the emergency department of the University Hospital Basel [30]. In patients with a ProCT level below 0.1 μg/l, the diagnosis of a bacterial respiratory tract infection is considered highly unlikely, and the GP is encouraged to look for viral or alternative causes. Accordingly, the use of antibiotics is discouraged. In patients with a ProCT level above 0.25 μg/l, a bacterial respiratory tract infection is considered the most likely diagnosis and the use of antibiotics is recommended. For ProCT levels from 0.1 to 0.25 μg/l, a bacterial infection is unlikely and antibiotic treatment is not advocated.

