The GP then informs the patient about antibiotic treatment by phone. Patients in whom antibiotics are given will be asked to use a delayed prescription or to come back to the practice to pick up the antibiotic there. For patients in whom antibiotics are withheld based on ProCT levels of 0.25 μg/l or below, a follow-up measurement of ProCT within 24 hours is mandatory. If the ProCT level on this initial follow-up is >0.25 mg/l or if it has increased by more than 50% from its initial value without clinical improvement of the patient, the use of antibiotics is recommended.

In the ProCT group, all patients treated with antibiotics will be reassessed at Day 3. Discontinuation of antibiotic treatment is recommended if the ProCT level has decreased at least to 0.25 μg/l or below.

GPs draw blood samples and document therapy at each follow-up visit. They also collect information on days with restrictions and days off work at 1 week (6–8 days) after randomisation for all patients. Medical students, blinded to treatment allocation of patients and to the goal of the trial, will conduct standardised follow-up interviews at 14 and 28 days by phone. The patient flow will be monitored according to current guidelines and in agreement with the CONSORT statement [43]. We will use Teleform^® ^(Cardwell, Cardiff, GB) for data entry.

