### Outcomes and hypotheses

The primary outcome is days with restrictions from ARTI within 14 days after randomisation. Secondary outcomes are antibiotic use in terms of antibiotic prescription rate and duration of antibiotic treatment in days, days off work and days with side-effects from medication within 14 days, and relapse rate from ARTI within 28 days after randomisation.

Our hypothesis is that the clinical outcome for patients with ARTI will be no worse under ProCT-guided treatment, but patients with ProCT-guided treatment will have lower total antibiotic use; specifically a 20% lower antibiotic prescription rate and a 20% shorter antibiotic duration compared to patients treated under the standard approach.

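### The superiority claim of lower antibiotic use is assigned only a per-protocol analysis, on a non-inferiority argument that does not apply to it

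*Protocol article*

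**What the plan says.** The Statistical analysis section of the protocol article opens with a caution: "With a non-inferiority trial, an intent-to-treat analysis is not necessarily conservative". For the primary outcome it concludes that "we will need to provide several intent-to-treat analyses under different assumptions about patients who do not complete the trial, and a per-protocol analysis". The next sentence deals with everything else: "Per-protocol analyses are planned for all secondary outcomes [44"]. No intent-to-treat analysis is named for any secondary outcome, and the per-protocol set is not defined.

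Under Outcomes and hypotheses, "Secondary outcomes are antibiotic use in terms of antibiotic prescription rate and duration of antibiotic treatment in days", followed by days off work, side-effect days and relapse. The hypothesis has two parts. The clinical outcome is to be no worse, and "patients with ProCT-guided treatment will have lower total antibiotic use". The size of that reduction is put at 20%, both for how often antibiotics are prescribed and for how long they are taken.

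The ProCT strategy is described under Data collection and management as a set of recommendations. At intermediate levels, "For ProCT levels from 0.1 to 0.25 μg/l, a bacterial infection is unlikely and antibiotic treatment is not advocated". At the Day 3 reassessment, "Discontinuation of antibiotic treatment is recommended if the ProCT level has decreased at least to 0.25 μg/l or below".

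**The concern.** The non-inferiority caution concerns claims that an arm is no worse, where deviations can dilute a real difference and make the arms look alike. It gives no support for leaving intent-to-treat out of a superiority claim. There, comparing the groups as randomised is the unbiased default, and dilution works against the claim.

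Antibiotic use raises a further difficulty, because adherence and outcome overlap. If per-protocol means that the advice was followed, a low-ProCT patient whose GP prescribes anyway is excluded because antibiotics were given. A patient treated beyond the stopping advice is excluded because treatment was long. Since entry requires an intention to prescribe, an untreated control might also count as a deviation. GPs overruling the result, which is one way an advice-based strategy can fail in practice, would then drop out of the estimate.

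Reduced antibiotic use is half of the objective under Study aims. The Discussion defends the open design partly because its biases should be conservative for prescription rate and duration. An adherence-based set would probably act in the opposite direction on those same outcomes.

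**Working it through.** **The plan's own figures.** For the primary outcome, with margin 1 day, SD 4, 90% power and one-sided 5% error, n = 2 × 4² × (1.645 + 1.282)² / 1² ≈ 274.1, so 275 per group. Then 275/0.90 = 305.6, so 306 per group and 612 in total. These match the article, and none depends on the analysis set of a secondary outcome.

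The stated ±6% for the antibiotic reduction was checked as 1.96 × √(p₁(1−p₁)/n + p₂(1−p₂)/n):
- 95% against 75%: 5.7 points (n = 275) and 5.4 points (n = 306).
- 90% against 70%: 6.5 and 6.1 points.

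The figure is plausible and serves as a yardstick.

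**Illustration.** The document gives no deviation rates, so all of these are assumptions:
- L: share of the ProCT arm at or below 0.25 μg/l, 20%, 40% or 60%.
- o: share of those treated anyway, 0 to 30%.
- s: share of controls untreated, 0 or 5%.
- u: share of high-ProCT patients untreated, 0 or 10%.

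Per-protocol is taken to mean that antibiotic use followed the allocated strategy.

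- Intent-to-treat difference = (1 − s) − [L·o + (1 − L)(1 − u)]
- Per-protocol difference = 1 − (1 − L)(1 − u) / [L(1 − o) + (1 − L)(1 − u)]

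| L | o | s | u | Intent-to-treat | Per-protocol | Shift (points) |
|---|---|---|---|---|---|---|
| 40% | 20% | 0 | 0 | 1 − 0.68 = 32.0 | 1 − 0.60/0.92 = 34.8 | +2.8 |
| 40% | 20% | 5% | 0 | 0.95 − 0.68 = 27.0 | 34.8 | +7.8 |
| 60% | 30% | 5% | 0 | 0.95 − 0.58 = 37.0 | 1 − 0.40/0.82 = 51.2 | +14.2 |
| 20% | 0 | 0 | 10% | 1 − 0.72 = 28.0 | 1 − 0.72/0.92 = 21.7 | −6.3 |

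Over the 60 combinations the shift runs from −6.3 to +14.2 points: upward in 42, zero in 3 and downward in 15. All 15 downward cases have 10% of high-ProCT patients untreated.

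**A wider share of low results.** Take L from 60% to 85%, o from 10% to 30%, s = 5% and u = 0.
- Lowest shift (L = 60%, o = 10%): intent-to-treat 0.95 − 0.46 = 49.0; per-protocol 1 − 0.40/0.94 = 57.4; +8.4.
- Highest shift (L = 85%, o = 30%): intent-to-treat 0.95 − 0.405 = 54.5; per-protocol 1 − 0.15/0.745 = 79.9; +25.4.
- With s = 0 the same range is +3.4 to +20.4.

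**Effect on the 20% hypothesis.** In the first set of combinations, the intent-to-treat difference is at least 23 points whenever L is 40% or more, so the hypothesised 20% is exceeded either way. With L = 20% the choice can decide the matter. At o = 0, s = 5%, u = 0 the differences are 15.0 points (intent-to-treat) and 20.0 (per-protocol). At o = 20%, s = 0, u = 10% they are 24.0 and 18.2.

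**The case against.** **The per-protocol set is undefined.** A reader might infer that the plan removes overruled patients and so inflates the reduction. The document does not say this. The ProCT output is a recommendation, and a GP who departs from it may still be within protocol. Deviations such as ineligibility, a missing ProCT result or a missed reassessment need not depend on prescribing. If the set means eligible completers, the mechanism disappears. This stands, and it limits the point to a risk. The mismatch between the stated reason and the superiority hypothesis remains under either meaning.

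**Some treatment after a low first result is protocol-consistent.** Patients from whom antibiotics are withheld are re-measured within 24 hours and may then be recommended treatment. The formulas have no such route and count every one of these treatments as overruling. The per-protocol contrast therefore need not simply reproduce the share of low first results.

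**The direction is not certain.** Excluding untreated high-ProCT patients lowers the per-protocol reduction. This stands, and the range above includes it.

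**Intent-to-treat is not literally ruled out.** The sentence says that per-protocol analyses are planned, not that they are the only ones. This is true, but the adjacent sentence names both sets for the primary outcome, so per-protocol only is the likelier reading.

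**Clinical secondary outcomes differ.** Relapse and days off work plausibly fall under the no-worse hypothesis, where the caution about intent-to-treat is relevant. This stands: per-protocol should not be demoted there. Nor does the document support supposing that overruled patients are the sicker ones.

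**Conclusion.** The point holds as a mismatch between analysis set and hypothesis. Antibiotic use carries a superiority claim, yet the only analysis named for it is per-protocol, and the only reason given concerns non-inferiority. If the set is defined by following the ProCT advice, exclusions depend on the outcome and the reduction is probably overstated. The shift is about −6 to +14 points in the main illustration and up to about +25 with 85% low results and 30% overruling, so it can exceed the stated ±6%. These sizes rest entirely on assumed rates and on an adherence-based definition. That the plan certainly excludes by outcome, or certainly inflates the effect, is not established.

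**What to change.** In the Statistical analysis section, name intent-to-treat as the main analysis for antibiotic prescription rate and antibiotic use, and state that any superiority claim on antibiotic use rests on it alone. Keep per-protocol as supportive, with its exclusions listed in advance and defined independently of whether, or for how long, antibiotics were taken. For days off work, side-effect days and relapse, report both intent-to-treat and per-protocol analyses, as for the primary outcome.

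This costs a few sentences. The sample size stays at 275, 306 and 612. The reported reduction in antibiotic use will probably be smaller. The article reports 213 patients recruited by April 2005, with recruitment planned to December 2005, so the change can be made before analysis. Analysing duration only in patients who receive antibiotics is a separate selection after randomisation, which this change does not remove.

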**Methods/Design:**

This is a randomised controlled trial in primary care with an open intervention. Adult patients judged by their general practitioner (GP) to need antibiotics for ARTI are randomised in equal numbers either to standard antibiotic therapy or to ProCT-guided antibiotic therapy. Patients are followed-up after 1 week by their GP and after 2 and 4 weeks by phone interviews carried out by medical students blinded to the goal of the trial.

Exclusion criteria for patients are antibiotic use in the previous 28 days, psychiatric disorders or inability to give written informed consent, not being fluent in German, severe immunosuppression, intravenous drug use, cystic fibrosis, active tuberculosis, or need for immediate hospitalisation.

The primary endpoint is days with restrictions from ARTI within 14 days after randomisation. Secondary outcomes are antibiotic use in terms of antibiotic prescription rate and duration of antibiotic treatment in days, days off work and days with side-effects from medication within 14 days, and relapse rate from the infection within 28 days after randomisation.

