### Randomisation

Allocation of patients to either treatment group is concealed by using a centralised randomisation procedure with a computer generated list produced by an independent statistician otherwise not involved in the trial. Randomisation is stratified by GP practice.

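### Randomisation is stratified by practice, but the main models omit practice, and the GP-based sensitivity analyses are confined to single-GP practices with at least 10 patients

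*Protocol article*

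**What the plan says.** All references are to the protocol article.

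- **Randomisation:** "Randomisation is stratified by GP practice". Patients are allocated individually through a central list. The abstract gives the ratio: they "are randomised in equal numbers either to standard antibiotic therapy or to ProCT-guided antibiotic therapy". Each practice can therefore contribute patients to both arms.
- **Statistical analysis, main models:** "All outcomes will be analysed by a generalised linear model, assuming an appropriate distribution for each outcome and using the same set of covariates". The list follows: "These covariates will be: age, sex, education and a baseline score of the degree of restricted activity reported by the patient". Neither practice nor GP is on it.
- **Statistical analysis, primary outcome:** a sensitivity analysis adds the GP as a random effect, but only for GPs "with only one GP per practice and with at least 10 patients per GP".
- **Statistical analysis, prescription rate:** for the confidence interval of the difference, "we will repeat this calculation using a method appropriate for a cluster sample, where each GP forms a cluster", with the same two restrictions.
- **Other secondary outcomes:** no analysis with a GP or practice term is described.
- **Sample size considerations:** at least 10 patients per practice, preferably 15, are wanted so that variability between GPs can be assessed.
- **Reason given:** in an earlier trial, GPs made little difference to what patients reported.

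**The concern.** Stratifying by practice, if it balances the arms within practices, takes between-practice variation out of the treatment contrast. A model without practice leaves that variation in the residual, so the reported standard error is larger than the design warrants. In a non-inferiority trial this widens the interval that is compared with the one-day margin.

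The sensitivity analyses do not repair this. They add the GP and at the same time remove every multi-GP practice and every GP with fewer than 10 patients. If the result differs from the main analysis, nobody can tell whether the model or the population caused it. If non-inferiority is missed there, lost numbers alone could be the reason.

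**Working it through.** **1. The plan's own figure.** Inputs from Sample size considerations: margin 1 day, SD 4 days, type I error 5%, power 90%. n = 2 × 4² × (1.645 + 1.282)² / 1² ≈ 274.1, rounded up to 275 per group at one-sided 5%. Then 275/0.90 = 305.6, so 306 per group and 612 in total. The stated sizes are reproduced, and this point does not alter them.

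**2. Effect of omitting practice on the primary outcome.** No ICC is given, so ρ is an assumption. With balance within practice and 275 analysed per group:

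- model SE without practice = 4 × √(2/275) = 0.341
- true SE = 0.341 × √(1 − ρ)
- ratio = 1/√(1 − ρ)
- type I error without practice = 1 − Φ(1.645 × ratio)
- power without practice = Φ((1 − 1.645 × 0.341)/true SE)
- power with practice = Φ(1/true SE − 1.645)

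| ρ (assumed) | SE ratio | Type I error without practice | Power without | Power with |
|---|---|---|---|---|
| 0 | 1.000 | 5.0% | 90.1% | 90.1% |
| 0.02 | 1.010 | 4.8% | 90.3% | 90.6% |
| 0.05 | 1.026 | 4.6% | 90.7% | 91.4% |
| 0.10 | 1.054 | 4.2% | 91.3% | 92.6% |

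A simulation of 50 practices with 11 patients each, balanced within practice (6,000 runs), agrees. At ρ = 0.05, type I error was 4.3% without practice and 4.8% with it, and power was 91.0% and 91.7%.

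**3. Who is lost in the sensitivity analyses.** The Participants section gives 53 GPs in 50 practices, so 47 to 49 practices have a single GP. Average recruitment is 612/50 = 12.2 per practice, close to the cut of 10. Recruitment was simulated with a cap of 20 per practice and 47 single-GP practices. Three patterns were assumed: equal expected recruitment, moderately uneven (gamma weights, shape 3) and strongly uneven (gamma weights, shape 1).

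| Patients | Pattern | Share kept | GPs kept | Power, one-sided 5% |
|---|---|---|---|---|
| 612 | equal | 81.1% | 37 | 87.3% |
| 612 | moderate | 77.9% | 30 | 86.1% |
| 612 | strong | 81.5% | 28 | 87.4% |
| 550 | equal | 72.2% | 31 | 80.1% |
| 550 | moderate | 72.6% | 26 | 80.3% |
| 550 | strong | 77.9% | 25 | 82.7% |

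Between 18.5% and 27.8% of patients are dropped.

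**4. Prescription rate: the direction is open.** The formula in step 2 assumes a practice effect shared by both arms. Enrolment requires that the GP already intends to prescribe, so control-arm prescribing may be close to universal and GP variation may sit mainly in the ProCT arm. As an illustration, assume 97% prescribing in the control arm, 80% in the ProCT arm, 6 patients per arm per practice, variation in the ProCT arm only, and GPs regarded as a random sample. Then

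plain SE / true SE = √[(0.0291 + 0.16) / (0.0291 + 0.16 × (1 + 5ρ))],

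which is 0.91, 0.84 and 0.74 at ρ = 0.05, 0.10 and 0.20. Here the plain interval is too narrow.

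**The case against.** The strongest reply is that little is at stake for the primary outcome. The error is conservative, power stays at or above the planned 90% in every row of the first table, and the authors give a reason to expect little variation between GPs in patient-reported outcomes. The gain also depends on balance within practice, and the article states no blocking. The 10-patient rule has a declared purpose, the study of variability between GPs, and the share of patients it excludes depends on assumed recruitment. With 35 active practices the average would be 612/35 = 17.5, and fewer would fall below 10. All of this stands, and it limits the size of the point. It does not explain why a random-intercept model should discard small practices, or why multi-GP practices must go when practice itself can be the term.

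A reader might also infer that every GP-based analysis treats the trial as a cluster sample. That is not so: the primary-outcome analysis uses a GP random effect, which is a sound way to reflect the stratum.

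A further tempting reading is that the cluster-sample method for prescribing is wrong in direction and inflates the interval. The article names no design effect. A cluster method built on within-GP differences is valid, and where GPs vary in the ProCT arm it captures variation that the plain analysis misses. Nor can one say that the main prescribing interval is too wide: step 4 shows that it may be too narrow.

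**Conclusion.** The point holds in a limited form. The stratification factor is missing from the main models, and for days with restrictions this makes the standard error about 1.0% to 2.6% too large at an assumed ICC of 0.02 to 0.05. The loss of power is 0.3 to 0.7 percentage points. Type I error is not inflated and the sample size is unaffected. These figures assume balance within practice and an effect common to both arms.

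The more practical weakness is the restriction on the sensitivity analyses. They alter model and population together and, under the assumed recruitment patterns, leave out about 18% to 28% of patients. For the prescription rate, neither the direction nor the size of any error in the main interval can be established from the article. What can be said is that the cluster method is not specified closely enough to exclude a between-cluster variance inflation, which would not suit a trial that randomises patients.

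**What to change.** 1. Add practice, as a random intercept or stratum, to the main models for all outcomes. Use all randomised patients, and in per-protocol analyses all patients in that set.
2. Keep the model without practice as the sensitivity analysis on the same patients, so that only the model changes.
3. Remove the single-GP and 10-patient restrictions from the GP-based analyses. With practice as the term, neither is needed.
4. Keep a cluster-type analysis for the prescription-rate difference. State that it respects the treatment contrast within practices, for example a practice-stratified risk difference with a practice-clustered robust variance, and that no between-cluster design effect is applied.

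The cost is a change of wording and one model term. Practice is already known for every patient from the randomisation, so no new data and no extra patients are needed.

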**Figure 2 F2:**
[figure not shown]
Flow diagram of recruited general practitioners.

From December 2004 GPs included in this study consecutively screen all eligible adults (aged 18 years or older) with symptoms (first experienced within the previous 28 days) of acute infection of the respiratory system. Inclusion criteria for patients are a consultation for common cold, pharyngitis, tonsillitis, rhinosinusitis, tracheo-bronchitis, otitis media, influenza, acute exacerbations of asthma or COPD, or community acquired pneumonia, the GPs intention to prescribe antibiotics on the basis of evidence-based guidelines, and written informed consent. Exclusion criteria for patients are antibiotic use in the previous 28 days, intravenous drug use, psychiatric disorders or inability to give written informed consent, not being fluent in German, severe immunosuppression (e.g. in HIV-infection, after solid organ transplantation or under chemotherapy), cystic fibrosis, active tuberculosis, and need for immediate hospitalisation. Study practices complete the trial after including 20 patients or at the anticipated end of the trial in December 2005.

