### Sample size considerations

This is a non-inferiority trial. We aim to show that on average ProCT-guided antibiotic management leads to at most one day more with restrictions than a standard approach. We consider a type I error rate of 5% and a type II error rate of 10% (i.e. 90% power) appropriate in this situation. In a previous trial in patients with acute respiratory tract infections (ISRCTN57824788), the standard deviation in the number of days with restrictions from ARTI was 4 days for those patients prescribed antibiotics. Given this previous estimate of the variability in the primary outcome, 275 patients are needed per treatment group [44]. Allowing for a loss to follow-up of 10% gives 306 patients per treatment group, or a total of 612 patients. This sample size will allow us to estimate the reduction in antibiotic use between the two arms to within ± 6%.

With a maximum of 20 patients recruited per practice we will probably need at least 35 participating general practices. To assess between-GP-variability in a sensitivity analysis, we will need a minimum of 10 patients (preferably 15) recruited per practice.

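### The fixed covariate set leaves out the inclusion diagnosis, which is already collected; adding it, fixed before allocation, would bring a modest gain in precision

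*Protocol article*

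**What the plan says.** The Statistical analysis section specifies a generalised linear model for every outcome, with a common set of covariates, and closes the list: "These covariates will be: age, sex, education and a baseline score of the degree of restricted activity reported by the patient". For the primary outcome, days with restrictions within 14 days, the model is a linear regression with normal errors.

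Diagnosis appears in three other places in the protocol article:

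- **Participants.** A qualifying diagnosis is an inclusion criterion. About nine are listed, starting with common cold and pharyngitis and ending with "acute exacerbations of asthma or COPD, or community acquired pneumonia".
- **Data collection and management.** The GP's baseline documentation covers "diagnostic procedures, diagnosis, co-morbidity and prescribed medication". The text describes this after the call that allocates the patient.
- **Randomisation.** The only stratification factor is the GP practice.

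The document gives no reason for including education and omitting diagnosis, and no figure for how strongly diagnosis predicts the outcome.

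**The concern.** The admitted conditions can be expected to differ in how long they restrict a patient. A baseline variable that predicts the outcome is worth adjusting for: it removes residual variance and corrects the estimate for chance differences in case mix between the arms. Here neither the randomisation nor the analysis model uses diagnosis, although the trial collects it.

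The primary question is whether the interval for the difference excludes one extra day with restrictions. Any avoidable width in that interval works against a conclusion of non-inferiority. Because the list is stated as closed and applies to every outcome, this is a choice the document makes, not a detail left to a later plan.

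**Working it through.** **Inputs from Sample size considerations.** The margin is one day ("ProCT-guided antibiotic management leads to at most one day more with restrictions than a standard approach"), the type I error 5% and the power 90%. The SD is 4 days ("the standard deviation in the number of days with restrictions from ARTI was 4 days"), and nothing says that it was adjusted for covariates. The true difference is taken as 0.

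**Step 1: reproduce the plan's figure.** n per group = 2 × SD² × (z for alpha + z for power)² / margin².

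- One-sided 5%: 2 × 16 × (1.645 + 1.282)² / 1² = 274.04, rounded up to 275. This matches "275 patients are needed per treatment group".
- With 10% loss: 275 / 0.90 = 305.6, so 306 per group and 612 in total, also a match.
- One-sided 2.5% would give 337 per group, so the plan was sized at one-sided 5%.

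The calculation takes no credit for any covariate, so leaving out diagnosis does not make it wrong.

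**Step 2: gain from diagnosis.** Let R² be the share of residual variance that diagnosis explains beyond the planned covariates. The document gives no value; the range below is assumed. To begin with, the planned covariates are taken to explain nothing, so the residual SD without diagnosis is 4.

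- Residual SD = 4 × √(1 − R²)
- SE of the difference = residual SD × √(2/275)
- Power = Φ(1/SE − z), with z = 1.645 (one-sided 5%) or 1.960 (two-sided 95% interval)

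Without diagnosis, SE = 4 × 0.0853 = 0.341 and 1/SE = 2.93.

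| R² (assumed) | Residual SD | Power, one-sided 5% | Power, 95% interval | Half-width of 95% interval (days) |
|---|---|---|---|---|
| 0 | 4.000 | 90.1% | 83.4% | 0.669 |
| 0.02 | 3.960 | 90.6% | 84.2% | 0.662 |
| 0.05 | 3.899 | 91.4% | 85.3% | 0.652 |
| 0.10 | 3.795 | 92.6% | 87.1% | 0.634 |

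From the unrounded values, the gain over R² of 0.02 to 0.10 is 0.5 to 2.5 points at one-sided 5%, and 0.7 to 3.6 points against the 95% interval.

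**Step 3: if the planned covariates already work.** Suppose they explain 20% of the variance (assumption). The residual SD is then 4 × √0.80 = 3.578, and power without diagnosis is 94.9% (one-sided 5%) or 90.6% (95% interval). Removing a further 2% to 10% of that residual variance gives 95.2% to 96.5%, or 91.2% to 93.2%. The gains shrink to about 0.3 to 1.6 points and 0.5 to 2.6 points.

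**Step 4: is an R² of this order plausible?** If a share p of patients has diagnoses averaging d more days of restriction, R² = p(1 − p)d²/SD². With p = 0.30 and d = 2 (both assumed), R² = 0.21 × 4/16 = 0.0525, before allowing for anything the baseline restriction score absorbs. With p = 0.10 and d = 1, it is 0.09 × 1/16 = 0.0056.

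**Step 5: chance imbalance.** In the same illustration (p = 0.30, d = 2), the SD of the between-arm difference in prevalence is √(0.3 × 0.7 × 2/275) = 0.039. That moves the estimate by 2 × 0.039 = 0.08 day (one SD), or about ±0.15 day over a 95% range, against a margin of one day.

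**Step 6: cost in degrees of freedom.** With 550 analysed and six parameters in the planned model (one per covariate, assumed), 544 residual degrees of freedom remain. Four diagnosis groups use 3, about 0.6%. Eight separate indicators would use 8/544 = 1.5%, and would bring roughly no gain if R² were below about 0.015.

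**The case against.** The strongest reply is that nothing here is an error. One covariate set is prespecified, and it contains the baseline measure closest to the primary outcome, the patient's own restriction score. That score may absorb much of what diagnosis would add. The case mix is also narrower than the list suggests, because every patient is one the GP intends to treat with antibiotics and those needing immediate hospitalisation are excluded. This stands, and it limits the point to one of efficiency with an unknown, probably modest, gain.

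A second reply concerns timing. The baseline documentation is described after allocation, the intervention is open, and a low ProCT result prompts the GP to look for viral or other causes. A diagnosis written down at that stage could depend on the arm, and adjusting for it could bias a comparison that is now unbiased. This stands against using whatever diagnosis is on the form. It does not stand against the diagnosis on which the patient was included: a qualifying condition is required for entry, so it must be settled before the call.

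A reader might go further and infer that the omission biases the treatment comparison, that the trial is undersized because of it, or that the precision given up is free and demonstrated. The document supports none of these. Randomisation keeps the estimate valid, and the interval already allows for chance imbalance. The 275 per group takes no credit for covariates. The share of variance explained is not given, and the gain is safe only if the diagnosis is fixed before allocation. Nor does the 83.4% result from omitting diagnosis: it comes from sizing at one-sided 5% and reporting a 95% interval, which is a separate matter.

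**Conclusion.** The point holds as a minor improvement. The covariate list leaves out a plausible prognostic factor that the trial already collects and that the randomisation does not balance by design. The gains in step 2 rest on an assumed further 2% to 10% of residual variance, 275 analysed per arm, an SD of 4 days and no true difference. They shrink as in step 3 if the planned covariates explain variance, and could be close to nil if the restriction score captures most of what diagnosis would add. The planned estimate remains valid and the stated sample size is unaffected.

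**What to change.** Add to the covariate list in the Statistical analysis section one prespecified grouping of the inclusion diagnosis, used for all outcomes. An example is: upper respiratory infection; tracheo-bronchitis or influenza; exacerbation of asthma or COPD; pneumonia. State in advance when groups are collapsed for outcomes with few events, such as relapse, and where each diagnosis then goes, influenza included.

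Define the covariate as the diagnosis the GP states at inclusion, before the allocation call and before any ProCT result, and have the study centre record it at the call. If that diagnosis is not available for patients already enrolled (213 by April 2005, according to the time plan), leave the primary model as it is and report the diagnosis-adjusted model as a prespecified sensitivity analysis.

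The cost is a short addition to the analysis section, about 3 degrees of freedom, and one more item to record at the call.
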